### Primary end points

The primary end point is the 3-year graft failure rate in HLA Ab + patients. Graft failure will be defined as restarting long-term dialysis or requiring a new transplant. Time zero starts at the time of randomisation, once the result of the HLA test is known. For those patients who are HLA Ab– at randomisation but become Ab + during a subsequent screening, time zero will be reset at the time of the positive test, and the follow-up time will be extended to allow for the 3-year end point.

### Secondary end points

The secondary clinical end points are:

• 3-year graft failure rates in all patients recruited to the trial

• Patient survival

• Rate of progression of graft dysfunction, as assessed by the change in the degree of proteinuria (PCR > 50) or the change in estimated GFR over 3 years

• Rate of biopsy-proven rejection over 3 years

• Rates of culture- or polymerase chain reaction-positive infection, biopsy-proven malignancy and DM

• Health economic analysis of outcomes

• Analysis of adherence and perceptions of risk for the biomarker-led care (BLC) groups

• The secondary scientific end points are:

• Changes in characteristics of HLA Ab and laboratory parameters of T and B cell phenotypes and responsiveness for the HLA Ab + groups

• Change in numbers and phenotype of circulating CD34+ cells for the HLA Ab + groups

## Trial design

This is a prospective open-labelled randomised marker-based strategy trial, with a standard control, where biomarker stratification is based on HLA Ab status. The biomarker-strategy design is appropriate for testing the clinical utility of a biomarker
[10]. Recruitment will take place in five British renal transplant units over 3 years, with recruits followed for at least 3 years. The trial design is shown in the flow diagram in Figure 
1, which shows the number of patients anticipated to be in each group by the end of the trial, based on sample size calculations, consent rates, eligibility and estimated attrition. Recipients of cross-match negative transplants aged 18 to 70, >1 year post-transplant with eGFR ≥ 30 will be asked to give consent for the screening/treatment process.

**Figure 1 F1:**
[figure not shown]
**OuTSMART flow diagram.** *Randomisation is performed using the results of a recruit’s first screening test. Those with donor specific antibodies (DSA) undergo no further screening as part of the trial (but serum will be stored for analysis of human leukocyte antigen antibody profiles later). †Those initially HLA Ab– undergo routine screening every 8 months. There is no second randomisation. A recruit allocated to blinded standard care (group C) who becomes HLA Ab + (black lines) will remain in a standard care group (group A1 or A2). If in the unblinded standard care group (D), they will change to unblinded biomarker-led treatment care (group B1 or B2) (orange lines). ‡ The numbers in each group are those anticipated at the primary end point. Ab, antibodies; DSA, donor-specific antibodies; HLA, human leukocyte antigen; MMF, mycophenolate mofetil; tac, tacrolimus.

The first stratification will be based on blood test screening for HLA Ab. Approximately 30% will be HLA positive, with approximately 70% negative. HLA Ab + patients will be further screened with single-antigen beads (SAB) to determine whether DSA are present (approximately will have 1/3 DSA and 2/3 non-DSA). Thus, biomarker stratification has three arms (DSA+, non-DSA + and HLA Ab–). The second stratification will be based on current immunosuppression to ensure balanced numbers already on tac or MMF in each group. The immunosuppression stratification has four groups: MMF only, tac only, both tac and MMF, and neither tac nor MMF. The third stratification factor will be the recruiting study site (five sites).

HLA Ab + patients will be randomised 1:1 into either blinded standard care (SC) or unblinded BLC. Patients in the former (groups A1 and A2 in Figure 
1) will be blind to their biomarker status and will remain on baseline immunotherapy, whereas the clinicians of patients in the latter (groups B1 and B2 in Figure 
1) will know their HLA Ab status and will be offered treatment. HLA Ab– patients will remain on their existing immunotherapy and randomised 1:1 into either the blinded (C) or unblinded group (D), with only the latter knowing their HLA Ab status. Both these groups will receive regular Ab status monitoring for the first 3 years. Those patients who become positive during subsequent screening rounds (approximately 10% per year) will be moved to the appropriate HLA Ab + groups (DSA + or non-DSA+) for final data analysis. All patients in group D found to be positive on the second or subsequent rounds will be offered the same treatment as those patients who were positive in the first screening round, and followed up for 3 additional years from the time they become positive. Thus, the maximum amount of time any single patient can remain in the study is 6 years. ‘New’ patients, randomised but initially HLA negative at baseline, will be included in the intended primary analysis of HLA positive groups at each successive 8 monthly screening round. The patient flow diagram according to CONSORT guidelines is provided as Figure 
2.

**Figure 2 F2:**
[figure not shown]
**Consort diagram for OuTSMART.** Ab, antibody; HLA, human leukocyte antigen.

### Sample size calculations

The primary purpose of this trial is to demonstrate superior outcomes using a defined treatment strategy compared to standard care for biomarker (HLA Ab) positive patients. Once superiority is demonstrated for HLA Ab + patients, it is also necessary to demonstrate non-inferior outcomes when comparing the unblinded screening strategy to the blinded standard of care for the entire patient population, including those HLA Ab–. The graft failure rate 3 years after screening has been chosen as a clinically relevant primary outcome. As a reference for power calculations, we have used the observed failure rates reported by Lachmann *et al*.
[8] for HLA Ab + and HLA Ab– patients. Since failure rates differ between DSA + and non-DSA + patients, sample size calculations have been carried out separately for these groups. Following these calculations, we estimated the number to be screened, based on expected dropout rates, expected screening results and eligibility criteria (see below). We based our estimates of the differences in primary outcome between the groups on, first, the results of our preliminary data from patients with CR treated with a similar regime as used here, and second, our assessment that large differences in primary outcome will be needed to make the screening programme cost-effective.

Hypothesis testing will be sequential
[11]. Superiority will be tested first in the HLA Ab + groups to demonstrate the efficacy of the treatment. If this analysis is significant, then non-inferiority will be tested for the entire population to demonstrate the clinical utility of the biomarker screening. We calculated the sample size needed to show the superiority of the treatment optimisation for biomarker-positive patients using the hypotheses as follows.

Hypothesis 1.1: HLA Ab + patients with DSA, randomised to standard care (A1) will show higher graft failure rates than patients randomised to biomarker-led care (B1).

We hypothesise that the experimental treatment will bring the failure rate of group B1 down to that of non-DSA patients in standard care (A2). Assuming a 30% failure rate for group A1 (as in
[8]), and a 16% failure rate for group B1, 139 patients per group will provide 80% power and 5% type I errors, for a two-sided test.

Hypothesis 1.2: HLA Ab + patients, with non-DSA, randomised to standard care (A2) will show higher graft failure rate than patients randomised to biomarker-led care (B2).

We hypothesise that the experimental treatment will bring the failure rate of group B2 down to that of biomarker negative patients in standard care (C). Assuming a 16% failure rate for group A2 (as in
[8]), and a 6% failure rate for group B2, 146 patients per group will provide 80% power and 5% type I errors, for a two-sided test.

The numbers enrolled in groups A and B include those patients initially enrolled in groups C or D who become HLA Ab + during re-screening.

We calculated the sample size needed to show the non-inferiority of all unblinded patients compared to all blinded patients as follows.

Hypothesis 2: All patients randomised to unblinded screening (combined groups B1 + B2 + D) will show equal or lower graft failure rates than all patients randomised to blinded screening (combined groups A1 + A2 + C), irrespective of biomarker status.

At the end of the trial, we expect 60% of patients to be in the HLA Ab– groups, 13% in DSA + groups and 27% in non-DSA + groups (after dropouts). Assuming a 6% failure rate in biomarker negative groups C and D, the estimated average failure rate of all blinded screening patients is 11.8% (that is, (6 × 0.6) + (16 × 0.27) + (30 × 0.13)). Similarly, the estimated average failure rate in the unblinded screening group is 7.3%. We have established a non-inferiority limit of 5% absolute difference, so that the unblinded group would be considered non-inferior with a failure rate of 16.8% or lower. For this purpose, 1,043 patients in each arm would provide 90% power and 2.5% (one-sided) type I errors.

We will keep recruiting until every group has acquired the number required to test both hypotheses. When calculating the number of patients to screen for eligibility and to recruit, the following assumptions were made: (1) 60% of patients under follow-up at each transplant centre will meet the eligibility criteria, (2) 10% will refuse consent, (3) the prevalence of HLA Ab in most transplant populations is 25% to 30%, (4) 6% of initially Ab– patients will become Ab + in each screening round and (5) 2% will drop out every screening round.

Based on these assumptions and a recruitment audit in participating centres, we have estimated that we need to assess eligibility for 4,672 patients and enrol 2,522 to ensure sufficient numbers are in each group at the primary end point to test both hypotheses. Figure 
1 shows the number of patients needed in each of the arms to reach the primary end point to test hypothesis 2, which is sufficient to test hypotheses 1.1 and 1.2 (the numbers in groups A and B include those patients initially enrolled in groups C or D who were found to be HLA Ab + during re-screening).

A recruitment audit has revealed that there is a very high chance of recruiting all the required patients from five participating centres within 3 years. We anticipate recruiting sufficient numbers of patients to all groups by screening round 3 or 4. Each centre is expected to recruit similar numbers of patients.

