### Statistical analysis

#### Primary analysis

Statistical analysis will be on an intention-to-treat and treatment-received basis. We will consider the patients who become positive during the follow-up in the appropriate group.

The proportion of graft failures for each of the groups is denoted by π_A1_, π_B1_, etc.

Superiority (hypothesis 1):

H_0_: π_A1_ = π_B1_ and π_A2_ = π_B2_

H_1_: π_A1_ ≠ π_B1_ and π_A2_ ≠ π_B2_

To test superiority for the primary outcome for the biomarker (HLA Ab) positive groups (hypotheses 1.1 and 1.2), we will use a two-sided *Z*-test at the 5% level of significance, and will calculate the 95% CI for the difference in the proportion of graft failures between the biomarker-led care and standard care groups. The biomarker-led care groups will be considered superior if the absolute *Z* > 1.96, and our assumptions with respect to the size of the differences will supported if the CI includes a positive difference in proportions of 14% for hypothesis 1.1, and 10% for hypothesis 1.2.

Non-inferiority (hypothesis 2):

H_0_: π_Unblind_ – π_Blind_ ≥ δ

H_1_: π_Unblind_ – π_Blind_ < δ

To test for non-inferiority of the unblinded groups compared to the blinded groups (hypothesis 2), we will carry out a one-sided *Z*-test at the 2.5% level of significance. We will conclude non-inferiority if H_0_ is rejected, and the corresponding upper bound of the 95% CI excludes the limit δ (set at 5% more failures in the unblinded groups).

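### The success rule for hypothesis 1, on which the test of hypothesis 2 depends, contradicts itself: the printed hypotheses do not settle whether one or both antibody strata must succeed

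*Protocol article*

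**What the plan says.** All references are to the protocol article.

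- **One comparison.** Under Primary end points: "The primary end point is the 3-year graft failure rate in HLA Ab + patients". The Primary objective likewise compares treated with control patients among all who test positive. The Abstract predicts failure of about 20% against under 10% for antibody-positive recruits as a single group.
- **Two tests.** Under Sample size calculations: "Since failure rates differ between DSA + and non-DSA + patients, sample size calculations have been carried out separately for these groups". For hypothesis 1.1 (DSA+, 30% v 16%), "139 patients per group will provide 80% power and 5% type I errors, for a two-sided test". For hypothesis 1.2 (non-DSA+, 16% v 6%), "146 patients per group will provide 80% power and 5% type I errors, for a two-sided test".
- **The condition for hypothesis 2.** The same section makes testing sequential: "If this analysis is significant, then non-inferiority will be tested for the entire population to demonstrate the clinical utility of the biomarker screening". The analysis is referred to in the singular.
- **The hypotheses.** Under Primary analysis, H0 states equality in both strata, and the alternative is "H_1_: π_A1_ ≠ π_B1_ and π_A2_ ≠ π_B2". Biomarker-led care is declared superior when the absolute Z exceeds 1.96, with 1.1 and 1.2 each tested two-sided at 5%. No division of the 5%, order between 1.1 and 1.2, or pooled test is given.

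**The concern.** There are two Z values but one decision. The text points in two directions on how to combine them:

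- H0 is an intersection, so a difference in either stratum makes it false. That points to one significant test being enough.
- H1 is also an intersection, so it holds only if both strata differ. That points to both being needed.

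The two are not complements. If treatment works in non-DSA+ patients only, or in DSA+ patients only, the truth lies in neither hypothesis. Such a result is realistic, since the plan assumes different failure rates in the two strata and expects about twice as many non-DSA+ as DSA+ patients. A result with 1.2 significant and 1.1 not could be reported as success or as failure of the primary hypothesis, and hypothesis 2 could be tested or not, from the same data.

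**Working it through.** **Inputs.** From Sample size calculations: rates of 30% v 16% (DSA+) and 16% v 6% (non-DSA+); 139 and 146 per group; 80% power; two-sided 5%; end-of-trial shares of 60% Ab–, 13% DSA+ and 27% non-DSA+; 1,043 per arm for hypothesis 2. No patient is in both strata at analysis, so the two tests are treated as independent.

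**1. The plan's own figures.** The arcsine formula is n = 2[(z₀.₉₇₅ + z₀.₈₀)/h]², with h = 2(arcsin√p₁ − arcsin√p₂).

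- 1.1: h = 0.3362; n = 2(2.8016/0.3362)² = 138.8, rounded up to 139.
- 1.2: h = 0.3281; n = 2(2.8016/0.3281)² = 145.8, rounded up to 146.

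Both reproduce exactly. With the pooled-variance Z formula, power at these sizes is 79.5% and 78.3%.

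**2. Expected group sizes.** 0.13 × 1,043 = 135.6, about 136 DSA+ per group. 0.27 × 1,043 = 281.6, about 282 non-DSA+ per group. As a consistency check, 0.60 × 1,043 = 626, against the 627 given for groups C and D under Expected duration of trial. The plan also says recruitment continues until every group has its required number, so DSA+ may be 139 rather than 136.

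**3. Either test suffices.** With both nulls true, the chance of at least one |Z| > 1.96 is 1 − 0.95² = 9.75%. This counts both directions, as the printed absolute-Z criterion does. Counting only results favouring biomarker-led care, it is 1 − 0.975² = 4.9% instead of 2.5%.

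**4. Both tests required.** The error is at most 5%, and joint power is the product of the two powers.

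| DSA+ / non-DSA+ per group | Arcsine | Pooled Z |
|---|---|---|
| 139 / 146 | 0.800 × 0.800 = 64% | 0.795 × 0.783 = 62% |
| 136 / 282 | 0.792 × 0.974 = 77% | 0.785 × 0.968 = 76% |
| 139 / 282 | 0.800 × 0.974 = 78% | 0.795 × 0.968 = 77% |

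For 80% joint power with non-DSA+ held at 282, the power needed for 1.1 is 0.80/0.974 = 82%, or about 147 DSA+ per group (arcsine).

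**5. One comparison in all Ab+ patients.** Pooling the plan's rates by its shares:

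- standard care: (30 × 0.13 + 16 × 0.27)/0.40 = 20.55%
- biomarker-led care: (16 × 0.13 + 6 × 0.27)/0.40 = 9.25%

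These match the Abstract's prediction. At 136 + 282 = 418 per arm, an unstratified pooled Z-test has 99.6% power. For a stratified risk difference:

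- difference = (136 × 0.14 + 282 × 0.10)/418 = 0.113
- variance = (136/418)² × (0.21 + 0.1344)/136 + (282/418)² × (0.1344 + 0.0564)/282 = 0.000576, so SE = 0.024
- power = Φ(0.113/0.024 − 1.96) = Φ(2.75), which is over 99%.

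**The case against.** The strongest reply is that the plan does contain a rule. The printed H1 needs both strata to differ, and the text speaks of superiority in the groups, in the plural. On that reading no adjustment is needed, the error is at most 5%, and joint power at the expected sizes is only 2 to 4 points below 80%. This partly stands: the text leans towards requiring both. It does not settle the matter, because the H0 printed beside it is already false if one stratum differs and the critical value is tied to no particular Z.

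It can also be said that such detail belongs in a statistical analysis plan. That would answer an omission. Here the article itself prints the hypotheses, the level, the criterion and the sequence, and they disagree.

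A reader might infer more than the document supports:

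- **That the 80% and 5% are wrong.** They are stated for 1.1 and 1.2 separately and reproduce. The plan states no joint power.
- **That the trial's power is 64%.** That holds only if both tests are required and non-DSA+ groups stop at 146; the plan expects about 282.
- **That the error of hypothesis 2 is inflated.** A prior condition can only lower the chance of a false non-inferiority claim, so its one-sided 2.5% stands.
- **That a pooled test is the only correct primary analysis.** The plan gives a reason for separate strata, namely their different failure rates.

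**Conclusion.** The point holds as a contradiction in the printed decision rule for the primary hypothesis. The sizing of 1.1 and 1.2 taken singly is correct. For hypothesis 1 as a whole, the pair of 80% power and 5% error is not delivered under either of the two readings the text invites:

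- **Either suffices:** 9.75% false claims when both nulls are true.
- **Both required:** error at most 5%, with joint power about 76–78% at 136–139 and 282 per group, and 62–64% at 139 and 146. This also caps the chance of reaching hypothesis 2, whatever its stated 90% power.

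A single stratified comparison, or a fixed sequence in which 1.1 alone decides whether hypothesis 2 is tested, would keep 5% with about 80% power or more, but the article specifies neither. The figures rest on the plan's assumed rates and shares, equal shares in the two arms, and independence of the strata. The contradiction itself rests on no numerical assumption. It matters because the rule cannot be credibly chosen once results are known.

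**What to change.** Before any unblinded analysis, state which result allows hypothesis 2 to be tested, and write H0 and H1 as complements for that rule. Two options are coherent:

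- **(a) Co-primary.** Require both 1.1 and 1.2, each at two-sided 5%. H0 becomes equality in at least one stratum; H1 stays as printed. Restate joint power as about 76–78% at the expected sizes and 62–64% at 139/146. This is closest to the printed alternative and costs only wording, unless the sponsor wants 80% joint power, which needs about 147 DSA+ per group with 282 non-DSA+.
- **(b) One comparison.** Test biomarker-led against standard care in all Ab+ patients, stratified by DSA status (for example a Mantel-Haenszel risk difference), at two-sided 5%. If it succeeds, test hypothesis 2, then 1.1 and 1.2 with multiplicity control such as Holm. This matches the Primary objective and Primary end points, has over 99% power at the expected sizes and needs no more patients. It does change the primary analysis, and a win overall need not show benefit in DSA+ patients, since 27 of every 40 Ab+ patients are expected to be non-DSA+.

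Under either option, align the Primary objective, Primary end points, Sample size calculations and Primary analysis sections with the chosen rule.

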### Statistical analysis

#### Primary analysis

Statistical analysis will be on an intention-to-treat and treatment-received basis. We will consider the patients who become positive during the follow-up in the appropriate group.

The proportion of graft failures for each of the groups is denoted by π_A1_, π_B1_, etc.

Superiority (hypothesis 1):

H_0_: π_A1_ = π_B1_ and π_A2_ = π_B2_

H_1_: π_A1_ ≠ π_B1_ and π_A2_ ≠ π_B2_

To test superiority for the primary outcome for the biomarker (HLA Ab) positive groups (hypotheses 1.1 and 1.2), we will use a two-sided *Z*-test at the 5% level of significance, and will calculate the 95% CI for the difference in the proportion of graft failures between the biomarker-led care and standard care groups. The biomarker-led care groups will be considered superior if the absolute *Z* > 1.96, and our assumptions with respect to the size of the differences will supported if the CI includes a positive difference in proportions of 14% for hypothesis 1.1, and 10% for hypothesis 1.2.

Non-inferiority (hypothesis 2):

H_0_: π_Unblind_ – π_Blind_ ≥ δ

H_1_: π_Unblind_ – π_Blind_ < δ

To test for non-inferiority of the unblinded groups compared to the blinded groups (hypothesis 2), we will carry out a one-sided *Z*-test at the 2.5% level of significance. We will conclude non-inferiority if H_0_ is rejected, and the corresponding upper bound of the 95% CI excludes the limit δ (set at 5% more failures in the unblinded groups).

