[4], who showed that their CR group with HLA Ab showed progressive deterioration of renal function prior to graft failure. The same progressive deterioration was seen in the control group of patients with HLA Ab, whose grafts did not fail. These data illustrate that CR is a time-dependent process in which progressive graft dysfunction precedes graft failure. Moreover, the time from development of HLA Ab to graft failure is highly variable in different people.

Separate studies have reported the prospective follow-up of outcomes in those with HLA Ab. Terasaki and Ozawa
[6] studied 2,231 patients. In a group of 479 with HLA Ab, the 2-year graft failure rate was 15%, compared to 6.8% in the 1,753 with no HLA Ab. This trial noted that the patients who failed within 2 years had worse renal function on testing than those that did not, consistent with the fact that CR is a progressive and time-dependent process and those that fail are at the end of this process. In another study, the same group
[7] reported that the 4-year survival rate for 1,329 patients, all with functioning transplants, was 58% for those with HLA Ab (158 patients) vs 81% for those without (806).

Lachmann *et al*.

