### Exploratory moderator analysis

Additionally, for all primary and secondary analyses, we will carry out multivariable analyses, using generalised linear models, to adjust for the effects of stratification factors (for example, the previous immunosuppression regime). In this case, we will use the corresponding odds ratio to evaluate the adjusted size of the differences between proportions, by transforming back the estimated odds ratio associated with the treatment group into absolute differences in proportions. If the results of the analysis of the primary outcome are significantly affected, the adjusted effects will be taken as final.

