### Procedures for assessing efficacy parameters

Graft failure is defined as the return to long-term dialysis or re-transplantation. This will be measured from the date of recruitment and will be reported for failure due to any cause. The date of restarting dialysis or re-transplantation will be recorded on the Case Report Form.

Deteriorating renal function will be determined by linear regression analysis of the serial MDRD eGFRs from the point of recruitment (like that used by Dudley *et al*.
[14]). Deterioration is defined as a negative slope. To be valid, the linear regression should yield an adjusted *r*^2^ ≥ 0.35 and have *P* ≤ 0.05 for the slope value. Stable renal function will be defined as serial MDRD eGFRs that are not significantly different from the horizontal baseline (that is, *P* > 0.05 on linear regression analysis). An improvement in renal function will be defined as a change in the slope so that it becomes positive. Serum creatinine levels and MDRD eGFR for the 12 months preceding recruitment and for the whole time patients are on the trial will be recorded on the CRF.

Proteinuria is defined by the PCR of a urine sample and is significant if >50. The PCR will be recorded on the CRF.

Acute rejection is defined by a combination of: (a) an acute rise in serum creatinine prompting a renal biopsy and (b) any pathology on the biopsy that meets the criteria for acute rejection, according to the latest BANFF criteria. The number of biopsies and the appropriate biopsy reports will be recorded on the CRF.

A full economic evaluation will adopt a National Health Service (NHS) perspective. The 3-year outcomes are the rates of: (1) graft failure, (2) patient survival, (3) graft dysfunction (see definition above), (4) acute rejection and (5) culture-positive infection, malignancy or diabetes, together with (6) EQ-5D, which is a patient-specific quality-adjusted life years (QALY) measurement. Cost-effectiveness will use (1) to (5) where (1) is the primary and the others are secondary outcomes. Cost-utility will be measured using (6) (the EQ-5D questionnaire). The net benefit per patient will be calculated by multiplying QALY by the assumed maximum willingness-to-pay for QALY (£20,000 per QALY) and subtracting the costs. The costs of all interventions will be obtained from Guy’s or estimated by identifying relevant categories of resource utilisation or measuring the volume of each category and multiplying by the average NHS resource costs

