In summary, this trial will identify a group of patients at high risk of premature transplant failure. Therapy will be optimised for these at-risk patients, many of whom will be identified before they have started to deteriorate clinically. As described above, the natural history of untreated CR is of progressive loss of function, usually at a predictable rate, leading eventually to complete loss of graft function. Depending on the initial creatinine level, the time to graft loss will be variable, but graft loss rarely occurs without this period of progressive loss of function. Lachmann *et al*.
[8] reported a constant rate of graft loss from the start of their study, so we expect that the rate of graft loss in our study will be constant in the standard care group. We predict that optimised immunotherapy will change the natural history of the condition, and lead to stabilisation of function in a significant proportion (50%) of those with HLA Ab. This will be visible in our analyses of the secondary end points. Hopefully the treatment will prevent the predicted graft loss in the first 3 years for this group and thus impact on the primary end point of the study.

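### A cheap improvement: the primary graft-failure tests (hypotheses 1.1 and 1.2) are unadjusted although baseline eGFR is collected and described as prognostic, which gives up some power, mainly for hypothesis 1.1

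*Protocol article*

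**What the plan says.** Under Primary analysis, the decision rule for the two superiority hypotheses uses crude proportions: "The biomarker-led care groups will be considered superior if the absolute *Z* > 1.96". The effect measure is also crude; the team "will calculate the 95% CI for the difference in the proportion of graft failures between the biomarker-led care and standard care groups".

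Under Exploratory moderator analysis, the article adds multivariable analyses "using generalised linear models, to adjust for the effects of stratification factors (for example, the previous immunosuppression regime" and so on. The stratification factors are antibody status, current tacrolimus/MMF use and site (Trial design; Synopsis). Kidney function is not one of them. The same section lets the adjusted effects replace the crude ones if the primary result changes significantly.

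Baseline eGFR and urine PCR are both collected (First visit). "Serum creatinine levels and MDRD eGFR for the 12 months preceding recruitment" are recorded as well (Procedures for assessing efficacy parameters).

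On prognosis, the Background reports from one cited cohort that "the patients who failed within 2 years had worse renal function on testing than those that did not". The Discussion says: "Depending on the initial creatinine level, the time to graft loss will be variable".

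**The concern.** If time to graft loss depends on starting function, then so does the chance of failing within a fixed 3-year window. Part of the spread in the binary outcome is then predictable before treatment starts. A crude comparison leaves that part in the error term; adjusting for it narrows the confidence interval around the same absolute difference, with the same patients.

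The article fixes both the test and the adjustment set, so this is not a detail left open for a later plan. What is at stake is power, chiefly in the DSA-positive comparison, which sits at about 80%. Hypothesis 2 is tested only if the superiority analysis is significant, so power lost there also makes it less likely that the screening strategy is tested at all.

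**Working it through.** **Inputs from Sample size calculations.** Hypothesis 1.1: "Assuming a 30% failure rate for group A1" against 16% in B1, and "139 patients per group will provide 80% power and 5% type I errors, for a two-sided test". Hypothesis 1.2: 16% in A2 against 6% in B2, 146 per group, same power and level. Expected shares at the end of the trial after dropouts: 13% DSA-positive and 27% non-DSA-positive, with 1,043 per arm for hypothesis 2.

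**Step 1: reproduce the stated sizes.** Arcsine formula: n = 2(1.960 + 0.842)² / h² = 15.70 / h², with h = 2·asin(√p1) − 2·asin(√p2).
- Hypothesis 1.1: h = 0.3362, n = 138.8, so 139.
- Hypothesis 1.2: h = 0.3281, n = 145.8, so 146.

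Both match exactly. The formula has no covariate term, so the sizing assumes an unadjusted test.

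**Step 2: numbers the plan implies.** 0.13 × 1,043 = 136 per arm DSA-positive; 0.27 × 1,043 = 282 per arm non-DSA-positive. Unadjusted power is Φ(h√(n/2) − 1.96):
- Hypothesis 1.1, n = 136: Φ(2.773 − 1.96) = 79%.
- Hypothesis 1.2, n = 282: Φ(3.896 − 1.96) = 97%.

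**Step 3: effect of adjustment.** If the covariate removes a share R² of the outcome variance, the effective size is n/(1 − R²). R² is an assumption; the documents give no value.

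| Assumed R² | H1.1, n = 139 | H1.1, n = 136 | H1.2, n = 146 | H1.2, n = 282 |
|---|---|---|---|---|
| 0 | 80% | 79% | 80% | 97.4% |
| 5% | 82% | 81% | 82% | 97.9% |
| 10% | 84% | 83% | 84% | 98.4% |
| 15% | 86% | 85% | 86% | 98.8% |
| 20% | 88% | 87% | 88% | 99.2% |

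**Step 4: simulation check.** 6,000 trials per setting at 139 and 146 per group, with one normal baseline covariate, comparing the crude Z-test (about 80% throughout) with a standardised risk difference from a logistic model. The Monte Carlo error is about √(0.8 × 0.2 / 6,000) = 0.5 points.

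| Odds ratio per SD | Control-arm C-statistic | H1.1 adjusted | H1.2 adjusted |
|---|---|---|---|
| 1.65 | 0.64 | 82% | 81% |
| 2.23 | 0.71 | 84% | 82% |
| 2.72 | 0.74 | 86% | 84% |
| 4.48 | 0.82 | 91% | 87% |

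With no prognostic value there was no gain. Under the null (odds ratio 2.72 per SD), the adjusted test rejected in 5.1% (30% failure) and 5.0% (16% failure). A separate run of 2,000 trials per setting gave 5.3% to 6.1%, against 4.5% to 5.0% for the crude test, so the level should be checked with the final model.

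**The case against.** The strongest reply is that nothing here is wrong. The unadjusted test in a randomised trial is valid, and the stated sizes give the stated power for it. That stands: this is an efficiency point.

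Several stronger readings are tempting, and the documents do not support them.
- A reader might infer that the article names eGFR or proteinuria as the main driver of graft loss. It does not. The closest sentence is in the Discussion and concerns initial creatinine. Proteinuria appears in the Background only as something from which the antibody-related risk was independent. Hence eGFR is the covariate to add, and PCR is optional.
- A reader might infer that both tests have only 80% power. The trial is sized for hypothesis 2, and the article says this suffices for the other two. At about 282 per arm, hypothesis 1.2 has little left to gain.
- A reader might expect power near 90%. That takes an R² of about 25%, which for hypothesis 1.1 corresponds to a C-statistic around 0.82. This is optimistic, and the eligibility floor of eGFR 30 removes the patients with the worst function.

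Two objections concern the fit of an adjusted analysis. First, patients who become antibody-positive later have time zero reset to the positive test, so a value taken at randomisation may be up to about 3 years old. It remains a valid pre-randomisation covariate, but it will predict less for them. Second, if hypothesis 1.2 had only 146 per group, it would expect 146 × (0.16 + 0.06) = 32 failures. Arm, eGFR, three immunosuppression terms and four site terms make nine coefficients, or fewer than four events each. Both points shape the fix; neither defeats it.

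**Conclusion.** The point holds as a cheap improvement. The primary tests are crude, the only stated adjustment leaves out kidney function, and the article itself treats kidney function as prognostic and collects it before randomisation.

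The size rests on an assumed R², since no prognostic strength is given. For 5 to 20%, hypothesis 1.1 gains about 2 to 8 points, reaching about 81-88%. At the implied numbers hypothesis 1.2 gains at most about 2 points. If eGFR turned out not to be prognostic in this population, the gain would be nil. Nothing in the documents supports a claim that the planned test is biased, invalid or mis-sized.

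**What to change.** Prespecify as the primary estimate for hypotheses 1.1 and 1.2 a standardised risk difference. Fit a logistic model with arm, continuous baseline eGFR (baseline PCR optional) and the stratification factors. Average its predictions back to the absolute difference in 3-year failure proportions and give a robust 95% CI. Base the 5% two-sided test on that estimate, and keep the crude Z-test as a sensitivity analysis. The target quantity, sample size and nominal level do not change.

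Define eGFR as the value at randomisation for every patient, including those who become antibody-positive later. State in advance how sparse site or immunosuppression levels will be pooled.

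Remove the rule under Exploratory moderator analysis by which adjusted effects become final depending on how much they change the primary result. One estimate should be named primary before the data are seen.

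The cost is plan wording and no new data. The downsides are the pooling, a simulation check of type I error if hypothesis 1.2 has only about 32 failures, and a smaller gain among late converters.
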